## Abstract

**Background:**

Type 2 diabetes mellitus is a major health threat worldwide. *Cosmos caudatus* is one of the medicinal plants used to treat type 2 diabetes. Therefore, this study aims to determine the effectiveness and safety of *C. caudatus* in patients with type 2 diabetes. Metabolomic approach will be carried out to compare the metabolite profiles between *C. Caudatus* treated diabetic patients and diabetic controls.

**Methods and design:**

This is a single-center, randomized, controlled, two-arm parallel design clinical trial that will be carried out in a tertiary hospital in Malaysia. In this study, 100 patients diagnosed with type 2 diabetes will be enrolled. Diabetic patients who meet the eligibility criteria will be randomly allocated to two groups, which are diabetic *C. caudatus* treated(U) group and diabetic control (C) group. Primary and secondary outcomes will be measured at baseline, 4, 8, and 12 weeks. The serum and urine metabolome of both groups will be examined using proton NMR spectroscopy.

**Discussion:**

The study will be the first randomized controlled trial to assess whether *C. caudatus* can confer beneficial effect in patients with type 2 diabetes. The results of this trial will provide clinical evidence on the effectiveness and safety of *C. caudatus* in patients with type 2 diabetes.

**Trial registration:**

ClinicalTrials.gov identifier: NCT02322268

## Background

Type 2 diabetes mellitus is one of the biggest health concerns in the world. In 2014, about 387 millions of people suffer from type 2 diabetes worldwide. The number is projected to rise to 592 million people by 2035 [1]. The prevalence of type 2 diabetes in Malaysia showed the same worrying trend. One in every five Malaysians age over 30 has type 2 diabetes [2]. Despite the drug prescription, a majority (78 %) of patients with type 2 diabetes in Malaysia still have poor glycemic control with mean HbA1C of 8.7 % [3]. Poor glycemic control is associated with an increased risk of diabetic microvascular complications including neuropathy, nephropathy and retinopathy, and macrovascular complications such as coronary heart disease [4].

Currently, the most common treatment for type 2 diabetes includes the prescription of oral anti-diabetic drugs such as metformin and sulphonylureas [5]. While the efficacy of sulphonylureas has been confirmed, their use is associated with side effects such as increased weight gain and elevated risk of hypoglycemia [6]. In addition, researchers have shown that long-term treatment with oral anti-diabetic drugs is ineffective in protecting the declining function of the pancreatic beta-cell [7, 8]. The deterioration of pancreatic beta-cell function is associated with the elevated oxidative stress in type 2 diabetic patients [9, 10]. Research indicated that oxidative damage was higher in patients with type 2 diabetes than healthy individuals [11]. Patients with type 2 diabetes had lower antioxidant capacity than healthy individuals [12]. Antioxidant potentially reduces the harmful effect of oxidative stress and consequently decreases the insulin resistance [13].

Medicinal plants have been used as traditional medicine for treating diseases, and their uses are considered safer than the oral anti-diabetic drugs [14]. The discovery of metformin, from the *Galega officinalis* has augmented the interest to quest for more natural products to treat diabetes [15]. *Cosmos caudatus*, or known locally as *Ulam Raja*, is a medicinal herb found in tropical countries [16]. It has been identified as one of the ten commonly used medicinal plants in Malaysia for treatment of type 2 diabetes [17]. *C. caudatus* contained a variety of bioactive compounds, such as ascorbic acid, quercetin, proanthocyanidin, chlorogenic acid and catechin [18–21]. *C. caudatus* has been reported to have an extremely high antioxidant capacity of about 2500 mg ascorbic acid equivalent antioxidant capacity (AEAC) per 100 g of fresh samples as compared to orange and guava which had 142 mg and 270 mg AEAC, respectively [22]. Its high antioxidant content may suggest its potential in reducing the oxidative stress [20].

In addition, *C. caudatus* have been shown to possess various medicinal benefits [16] including anti-diabetic [23], antihypertensive [24] and anti-inflammatory effect [25] in animal studies. Recent pre-clinical study in rats indicated a significantly reduction in fasting blood glucose, and a significant improvement in lipid profile after 4 weeks of supplementation [23]. Preliminary study in healthy volunteers has shown that there was a steady reduction in the postprandial blood glucose after consuming rice and fresh *C. caudatus* (unpublished data). However, the effect of *C. caudatus* in patients with type 2 diabetes remains unclear.

Metabolomics is an unbiased approach to measure metabolites disturbance within a biological system at a given time [26]. The profiling of these metabolite can provide detailed information on the metabolic pathways [27]. Additionally, metabolites levels are influenced by environmental factors such as diet and lifestyle factors [28]. Therefore, by using metabolomics approach, it provides a clearer understanding of the effect of *C. caudatus* in patients with type 2 diabetes.

The objective of this trial is to investigate the effectiveness and safety of *C. caudatus* in patients with type 2 diabetes by addressing the following hypothesis (1) *C. caudatus* supplementation will improve the glycemic status in patients with type 2 diabetes (2) *C. caudatus* supplementation will improve inflammation marker, oxidative stress marker and lipid profile in patients with type 2 diabetes (3) *C. caudatus* supplementation is safe and will not result in adverse effects (4) the therapeutic effect of *C. caudatus* will result in changes in urine and serum metabolome.

## Methods and design

### Trial design

This is a single center, randomized, parallel-controlled clinical trial. A flow chart of the study protocol is shown in Fig. 1. This study will be conducted at a tertiary government hospital, Malaysia.

**Fig. 1 Fig1:**
[figure not shown]
Trial flow chart

### Ethical approval

The study protocol has been approved by the Ethics Committee for Research involving Human Subjects Universiti Putra Malaysia (JKEUPM) (FPSK_Ogos (13)05), Herbal Medicine Research Centre, Institute for Medical Research Malaysia (version 1, 8/2014) and Medical Research and Ethics Committee Ministry of Health Malaysia (NMRR-13-1344-18177). This protocol will be conducted in compliance with Helsinki declaration.

### Randomization

Patients with type 2 diabetes will be randomly allocated to either *C. caudatus* (U) group or control (C) group. The permuted block randomization (block of 4 and 6) will be used in this study. However, researchers will be blinded to the size of each block to reduce the selection bias. All laboratory personnel will also blinded to the group allocation.

### Sample size

A total of 50 patients are required in each group to detect a significant mean difference of 1 % HbA1C [29], 1.75 % standard deviation [29], 95 % confidence level and 80 % power, with additional drop-out rate of 30 %.

### Study population

Patients with type 2 diabetes will be recruited from the outpatient medical clinic at tertiary hospital. The diagnosis of diabetes will be based on the medical record of the tertiary hospital. Eligible diabetic patients will be enrolled in the study and written informed consent will be obtained prior to recruitment at the medical clinic of the tertiary hospital.

### Inclusion criteria

Men and women between the age of 30–65 years old who have confirmed diagnosis of type 2 diabetes for more than 6 months, last HbA1C value greater than 7 %, Body Mass Index (BMI) between 18.5 and 40 kg/m^2^, treated with stabilized dose of oral anti-diabetic drugs and expected to remain on this oral anti-diabetic drugs throughout the duration of the study.

### Exclusion criteria

Patients with any of the following criteria will be excluded: 1) pregnant and lactating; 2) have any gastrointestinal disorder that interferes the bowel function, severe hepatic or renal disease (dialysis), an infection that requires antibiotics within three weeks; 3) on insulin regimen; 4) Individuals on the anticoagulant drugs such as warfarin and aspirin.

### Intervention

#### Diabetic *C. caudatus* treated (U) group

The *C. caudatus* seeds were obtained from the Institute of Bioscience, Universiti Putra Malaysia (UPM) and planted at the Universiti Putra Malaysia Agricultural Park. A voucher specimen (No. SK 2400/14) has been deposited in the herbarium, Biodiversity Unit, Institute of Bioscience, Universiti Putra Malaysia. Fresh *C. caudatus* will be provided to the *C. caudatus* treated (U) group twice a week for 8 weeks. The *C. caudatus* will be vacuum packed in a zip-lock bag before distribution. Patients in *C. caudatus* treated (U) group will be asked to consume raw *C. caudatus* leaves (15 g) daily together with one of the main meal (either lunch or dinner) for 8 weeks.

*C. caudatus* supplementation will be given simultaneously with the usual diabetes care that includes maintenance of the oral anti-diabetic drugs dosage and compliance with the dietary and physical activity recommendations. In addition, patients in *C. caudatus* treated (U) group will be advised to perform self-monitoring blood glucose. Glucometer and strips will be given to the patients to record three values daily (after fasting, before a meal and two hours after a meal). All the patients will be educated on how to use the glucometer.

#### Diabetic control (C) group

The diabetic control (C) group will be asked to abstain from consuming *C. caudatus* for 8 weeks . Both groups will be given standard lifestyle interventions which include medical nutrition therapy and physical activity enforcement). In addition, both groups will be educated for the concepts of carbohydrate exchange and serving sizes. Patients in diabetic control (C) group will be encouraged to eat the same serving of fruits and vegetable as the *C. caudatus* treated (U) group. Likewise, patients in diabetic control (C) group will be advised to perform self-monitoring blood glucose. Glucometer and strips will be given to both groups to record three values daily (after fasting, before a meal and two hours after a meal). All the patients will be educated on how to use the glucometer.

### Adherence

To check patients’ compliance during the 8 weeks, the researcher will interview them weekly by telephone. In *C. caudatus* treated (U) group, patients will be interviewed to discern whether they were consuming *C. caudatus* and to address all their concerns. In diabetic control (C) group, phone calls are made weekly to emphasize the importance of lifestyle modification.

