### Patient safety

Patients will be monitored weekly during the study period and all the occurrence of the adverse events will be assessed by patient interviews. All anticipated adverse events such as loose stools, abdominal discomfort, bloating, flatulence, sign of hypoglycemia, sign of hyperglycemia will be recorded. Additionally, liver profile and renal profile will be measured at every visit.

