## Discussion

Type 2 diabetes is a common chronic disease worldwide. Medicinal plants are gaining tremendous resurgence of interest among researchers recently because of their health benefits [14, 34]. *C. caudatus* is widely consumed among the local Malays in South East Asia and its potential medicinal benefits have been reported [16]. The strength of this trial is that, it is the first randomized controlled trial to determine the effectiveness of *C. caudatus* on the outcomes measurement such as glycemic status, lipid profile, oxidative stress marker, and inflammation marker which are important parameters in patients with type 2 diabetes.

To the best of knowledge, there is no established data on herb-drug interaction of *C. caudatus*. Therefore, an interim analysis will be carried out to monitor the safety of consuming *C. caudatus* throughout the study. The results of this trial will provide clinical evidence on the effectiveness and safety of *C. caudatus* supplementation in patients with type 2 diabetes. Moreover, metabolomics is a powerful tool to study the altered metabolism, identify short-term changes in biological fluids and serve as biomarker detection [26]. Metabolomics approach used in this study will fill in the gap and provide a better understanding of metabolite profile following the supplementation of *C. caudatus*. Therefore, results from this study will contribute to the knowledge on the therapeutic effect mechanism of *C. caudatus*.

To date, the most commonly used metabolomics technologies for metabolomics study are nuclear magnetic resonance (NMR) spectroscopy, and mass spectrometry (MS) such as liquid chromatography-MS (LC-MS) and gas chromatography-MS (GC-MS) [26]. GC-MS and LC-MS are robust technologies that offer high sensitivity in metabolites detection [26]. However, both of the techniques have some drawbacks including relatively slower acquisition time, requires sample derivatization (GC-MS), consumption of sample (both LC-MS and GC-MS), chromatography can drift during a sample run, which makes data processing difficult (LC-MS), and peak assignment is a major challenge (LCMS) [35, 36]. On the other hand, NMR offers some advantages such as its ability to provide high-resolution spectra, requires relatively simpler sample preparation hence more rapid analysis and more importantly non-destructive of the sample. However, NMR-based metabolomics has a lower sensitivity compared to MS [35–37].

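### Weekly telephone lifestyle reinforcement is stated for the control arm only, so the HbA1C comparison mixes the plant with a difference in call content

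*Protocol article*

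**What the plan says.** All of this is in the protocol article.

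- **Diabetic control (C) group:** "Both groups will be given standard lifestyle interventions which include medical nutrition therapy and physical activity enforcement". Both arms are also taught carbohydrate exchange and serving sizes. Controls are asked to avoid the plant for 8 weeks.
- **Intervention, treated (U) group:** usual diabetes care continues, including compliance with the diet and activity recommendations.
- **Adherence, general statement:** "To check patients’ compliance during the 8 weeks, the researcher will interview them weekly by telephone".
- **Adherence, treated arm:** "patients will be interviewed to discern whether they were consuming *C. caudatus* and to address all their concerns".
- **Adherence, control arm:** "In diabetic control (C) group, phone calls are made weekly to emphasize the importance of lifestyle modification".
- **Patient safety:** patients are monitored weekly and "all the occurrence of the adverse events will be assessed by patient interviews", with no distinction by arm. Liver and renal profiles are measured at every visit.
- **Procedure:** all subjects complete a dietary history and the IPAQ at each follow-up.
- **Primary outcome and Statistical analysis:** the primary outcome is change in HbA1C. Changes are compared between arms with an independent t-test, and no adjustment for diet or activity is stated.
- **Discussion:** there is no placebo and patients are not blinded. The plant "is widely consumed among the local Malays in South East Asia".

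**The concern.** The evident intention is that the two arms share everything except the plant: same lifestyle programme, same education, same call frequency. The Adherence section departs from this by giving the calls a different purpose in each arm. As written, controls get up to eight weekly reminders about lifestyle, and the treated arm gets an intake check and an open invitation to raise concerns.

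The protocol itself treats nutrition therapy and physical activity as part of diabetes care, so extra reinforcement in one arm is a plausible influence on HbA1C, weight and lipids. The planned comparison cannot separate it from the plant. A null result could reflect better lifestyle in controls, and a positive one could partly reflect support in the treated arm. The lack of a placebo is hard to avoid with a raw leaf, and the article acknowledges it. Different call content is avoidable.

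**Working it through.** **Step 1: compare the arms as the text describes them.**

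| Element | Treated arm | Control arm |
|---|---|---|
| Background lifestyle programme | Same | Same |
| Call frequency | Weekly, 8 weeks | Weekly, 8 weeks |
| Stated call content | Plant intake, patients' concerns | Importance of lifestyle modification |
| Weekly lifestyle reinforcement | Not stated | Stated |
| Weekly question on plant intake | Stated | Not stated separately; covered at most by the general compliance sentence |
| Weekly adverse-event interview | Stated for patients generally | Stated for patients generally |
| Dietary history and IPAQ at follow-ups | Yes | Yes |

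The stated differences lie in the call-content rows. Adverse-event interviews and visit-based diet data are described identically for both arms.

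**Step 2: what the comparison then estimates.** Let p be the reduction in HbA1C due to the plant, s any reduction due to the treated arm's call content, and b any reduction due to the control arm's call content. The difference in mean change estimates p + s − b. It equals p only if s = b. The document gives neither s nor b, so the sign and size of s − b cannot be derived.

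**Step 3: illustration of how much it could matter.** No figure in the plan is at stake here, so there is none to reproduce. Inputs from the Sample size section: difference 1 %, SD 1.75 %, 50 per arm. The 95 % confidence level is taken as two-sided 5 %. The article's analysis set is all randomized patients with a baseline blood test, with last observation carried forward, so 50 per arm is the relevant number. **Assumption:** s = 0 and b between 0.1 and 0.4 points.

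Standardized difference d = (1 − b)/1.75. Noncentrality = d × √(50/2) = 5d. Degrees of freedom 98, critical t = 1.984, power from the noncentral t distribution.

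| b | Observed effect | d | Noncentrality | Power |
|---|---|---|---|---|
| 0 | 1.0 | 0.571 | 2.857 | 80.8 % |
| 0.1 | 0.9 | 0.514 | 2.571 | 72.1 % |
| 0.2 | 0.8 | 0.457 | 2.286 | 61.9 % |
| 0.3 | 0.7 | 0.400 | 2.000 | 50.8 % |
| 0.4 | 0.6 | 0.343 | 1.714 | 39.7 % |

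**Step 4: the opposite direction.** With b = 0 and s = 0.1, the observed effect is 1.1, noncentrality is 5 × 1.1/1.75 = 3.143 and power is 87.5 %. The plant would then be credited with 0.1 points that came from the calls. The table in Step 3 is therefore one side of a two-sided uncertainty, not a forecast.

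**The case against.** The strongest reply is that this is a difference of emphasis on top of a shared programme. Both arms receive the lifestyle intervention, the treated arm is expected to follow the same recommendations, and call frequency is matched. The Adherence section is a short summary, and nothing in it says that lifestyle is excluded from the treated arm's calls. Diet and activity are measured in both arms, so a differential change could be seen. The more likely bias is toward no effect, which would not manufacture a positive result. The article already concedes that bias is possible.

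Much of this stands, and it limits the size of the problem. It does not remove it. The article does not merely omit call content; it states a purpose for each arm, and the purposes differ. Seeing a lifestyle difference in questionnaire data does not correct the primary t-test. Bias toward no effect still harms a trial meant to show whether the plant works, and the direction is not certain.

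Two stronger readings are tempting, and the text does not support them.

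- *That adverse events are collected differently by arm.* Patient safety sets weekly monitoring and interviews for patients without distinction, lists the same anticipated events for all, and adds laboratory safety at every visit. What can be said is only that concerns are explicitly invited in one arm and that the control calls are not stated to carry the adverse-event questions.
- *That control-arm intake of the plant goes unchecked.* The opening sentence of Adherence covers compliance of patients in general, and all subjects give a dietary history at follow-up. The gap is that no weekly abstention question is spelled out for controls.

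**Conclusion.** The point holds in a limited form. Followed as written, the plan adds an avoidable co-intervention difference to an unblinded comparison: weekly lifestyle reinforcement in one arm, intake checking and support in the other. The HbA1C contrast therefore does not isolate *C. caudatus*.

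The document determines neither the net direction nor the magnitude. The power figures (about 81 % falling to between 72 % and 40 % at 50 per arm) rest on an assumed call effect of 0.1 to 0.4 points in controls, none in the treated arm, a true plant effect of 1 %, SD 1.75 % and a two-sided 5 % test. They show that even a small unintended effect would matter against the planned difference; they do not estimate that effect.

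Unequal adverse-event or dietary data collection is not established and forms no part of this conclusion. Because the shared lifestyle programme limits the imbalance, this is a change that should be made rather than a flaw that invalidates the trial.

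**What to change.** Use one common weekly call script in both arms, containing:

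1. the lifestyle message, delivered identically in both arms;
2. the same question on *C. caudatus* intake, read as compliance in the treated arm and as abstention in the control arm;
3. the adverse-event checklist from Patient safety, asked in the same words and order, with the same open question about concerns.

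Reword the Adherence section to describe this single script, so that it agrees with the shared lifestyle intervention under Diabetic control (C) group and with the weekly interviews under Patient safety.

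The cost is a revised script and slightly longer calls. The calls are already planned weekly in both arms, so no additional visits are needed.

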### Patient safety

Patients will be monitored weekly during the study period and all the occurrence of the adverse events will be assessed by patient interviews. All anticipated adverse events such as loose stools, abdominal discomfort, bloating, flatulence, sign of hypoglycemia, sign of hyperglycemia will be recorded. Additionally, liver profile and renal profile will be measured at every visit.

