We used NMR in this study as NMR-based metabolomics can detect many different metabolites simultaneously such as carbohydrate, amino acids, organic and fatty acids, amines and lipids. In addition, NMR-based metabolomic have shown high reproducibility and identification of the metabolites is relatively easy due to a good library of spectra [36]. The most prominent metabolites in the ^1^H NMR blood serum spectra are fat (methylene- and methyl-moieties from the lipoproteins), amino acids, lactate and glucose [38]. Meanwhile, creatinine, creatine, trimethylamide N-oxide, dimethylamide, citrate and lactate are the most significant metabolites found in the ^1^H NMR urinary spectra [39]. Recently, studies have revealed that there is a change in the amino acid metabolism in addition to the changes in glucose and fatty acid metabolism in patients with type 2 diabetes . Raised branched-chain amino acids including leucine, valine, isoleucine and glycerol were associated with the insulin assistance [40]. In the current study, NMR-based metabolomics is used to investigate the metabolic perturbation due to *C. caudatus* supplementation in patients with type 2 diabetes. To complement the current study, future studies involve MS-based metabolomics would provide further insight into the fatty-acid profiling in patients with type 2 diabetes.

However, there are limitations in this trial. Placebo is not used in this study. The reason is because there is no identical vegetable that can mimic the taste of *C. caudatus*. In addition,, there is also no blinding among the patients because they would know once they allocated in the treatment arm as they will receive the supplementation of *C. caudatus*. Therefore, the possibility of bias cannot be ruled out. In conclusion, findings from this study will provide significant evidence of using *C. caudatus* as an adjuvant therapy in patients with type 2 diabetes.

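### Hypoglycaemia is measured by patient interview alone, although both arms already record three glucometer values a day that could document low readings

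*Protocol article*

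**What the plan says.** **Measure of harm.** Under Patient safety, "Patients will be monitored weekly during the study period", and adverse events are "assessed by patient interviews. All anticipated adverse events such as loose stools, abdominal discomfort, bloating, flatulence, sign of hypoglycemia". Signs of hyperglycaemia follow in the same list. The section then adds liver and renal profiles at every visit, and Secondary outcomes lists these two as the safety parameters.

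**Glucose readings already planned.** The section on the control group says "Glucometer and strips will be given to both groups to record three values daily": fasting, before a meal and two hours after a meal. The section on the treated group says the same. Self-monitoring is advised, and all patients are taught to use the meter. No section says how the readings are collected or whether they feed into safety.

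**Background treatment.** Patients take a stabilised dose of oral drugs and are "expected to remain on this oral anti-diabetic drugs throughout the duration of the study". Insulin users are excluded; sulphonylurea users are not. The Background section says of sulphonylureas that "their use is associated with side effects such as increased weight gain and elevated risk of hypoglycemia".

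**Use of the safety data.** The third hypothesis in the Background section is that the supplement is safe and free of adverse effects. The Discussion says that herb-drug interaction data are not established, and plans an interim analysis to monitor safety for that reason.

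**Blinding.** The Discussion states that "there is also no blinding among the patients". Under Randomization, "All laboratory personnel will also blinded to the group allocation"; blinding of whoever conducts the interviews is not stated.

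**The concern.** Hypoglycaemia is the most foreseeable glucose-related harm when a plant meant to lower glucose is added to oral drugs held constant. It is also the one listed harm, apart from hyperglycaemia, for which the trial already plans frequent numerical readings. Interview depends on the patient noticing an episode and remembering it at the weekly contact. A low value without recognised signs need not surface there.

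The hypothesis is one of no harm, so missed events favour the hoped-for conclusion. If a share of lows goes unreported equally in both arms, any true difference shrinks by that share, and a small number of reports excludes less than it seems to. The interim safety analysis would inherit the same gap.

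**Working it through.** The plan gives no figure for hypoglycaemia, so there is none to reproduce. The check has two parts.

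**1. What is measured, and by what**

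- Loose stools, abdominal discomfort, bloating and flatulence: interview. This is the ordinary method and is adequate.
- Liver and renal function: laboratory tests at every visit. Adequate, but they do not detect hypoglycaemia.
- Fasting glucose: laboratory value at baseline and weeks 4, 8 and 12. Four fasting samples cannot stand in for daily readings.
- Hypoglycaemia: interview, recorded as a sign.
- Meter values: 3 per day × 56 days (8 weeks) = 168 planned per patient, or 168 × 50 = 8,400 per arm with full adherence. They appear neither under Patient safety nor among the secondary outcomes.

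**2. Illustration of what under-detection would do**

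Let s be the share of patients with a meter-detectable low whom the interview identifies, taken as equal in both arms. It is an assumption, shown from 0.3 to 1.0; the documents do not give it.

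*No reports in the treated arm.* The one-sided 95 % upper limit on the reported share is 1 − 0.05^(1/n). Dividing by s gives the limit on the true share. Here n = 50 is the planned arm, and n = 35 is 50 × 0.70, after the 30 % drop-out in Sample size.

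| s | n = 50 | n = 35 |
|---|---|---|
| 1.0 | 5.8 % | 8.2 % |
| 0.5 | 0.0582 / 0.5 = 11.6 % | 0.0820 / 0.5 = 16.4 % |
| 0.3 | 0.0582 / 0.3 = 19.4 % | 0.0820 / 0.3 = 27.3 % |

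The n = 35 column is pessimistic, because patients who drop out still contribute reports until they leave.

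*A true difference between arms.* Assume true shares of 30 % (treated) and 10 % (control), again not from the documents. The reported difference is s × (30 − 10) points. Power is that of a two-sided Fisher exact test at 0.05 with 50 per arm.

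| s | Reported shares | Difference | Power |
|---|---|---|---|
| 1.0 | 30 % v 10 % | 20 points | 64 % |
| 0.8 | 24 % v 8 % | 16 points | 49 % |
| 0.5 | 15 % v 5 % | 10 points | 24 % |
| 0.3 | 9 % v 3 % | 6 points | 9 % |

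The plan specifies no between-arm test of hypoglycaemia, so the power column only gauges the loss of information.

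**The case against.** The strongest reply is that the article is silent about the meter values and does not set them aside. A low reading may count as a sign, patients may mention it at interview, and they see their own readings, so s near 1 is plausible. A glucose threshold, a question script and the handling of meter logs are details that a condensed article may leave to the full protocol. Much of this stands. A reader might infer that the plan discards the readings; no section says so. Nor is the absence of a threshold or script an error in itself. What remains is that the article does name a measure for hypoglycaemia, and that measure is interview.

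A reader might also infer that safety rests wholly on self-report. It does not: liver and renal profiles are laboratory measures, and interview is right for the gastrointestinal events.

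A third tempting inference is that unblinded patients and unequal questioning will bias the comparison. The Adherence section does describe different calls: consumption and concerns in the treated arm, while in the control arm "phone calls are made weekly to emphasize the importance of lifestyle modification". But it does not say that these calls are the adverse-event interviews. If they were, the likelier result would be more reports in the treated arm, not a hidden excess. The Discussion already acknowledges possible bias, and none of the figures above depends on unblinding.

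Finally, the risk is moderated by excluding insulin users and requiring HbA1C above 7 %, so 30 % v 10 % may be too high. At an assumed 10 % v 2 %, Fisher power is only 19 % even with perfect detection; sample size limits that comparison before the interview does. This is fair, and is why the figures are illustrations only.

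**Conclusion.** The point holds for hypoglycaemia only, as an optional improvement. The plan names interview and a reported sign as the measure while both arms collect daily glucose values that bear directly on the same harm. Lows that are not recognised or recalled can therefore be missed in the test of the safety hypothesis and in the interim safety analysis.

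The size of the gain is unknown from the documents. Under the assumed range of s, with no reports among 50 treated patients, the upper limit runs from 5.8 % to 19.4 %; at s = 1.0 there is no loss. These figures rest on equal detection in both arms and on assumed rates, and they are not estimates of what the trial will lose. The primary HbA1C outcome is unaffected.

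**What to change.** In Patient safety, add one measure: the number of patients in each arm with at least one recorded meter value below a glucose threshold fixed in advance, reported with the number of readings available in each arm. Include it in the interim safety analysis. Keep interview-reported signs alongside, because tests tied to fasting and meals miss night-time episodes. Leave the liver and renal profiles, and interview for gastrointestinal complaints, as they are.

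The cost is a sentence or two of protocol text, one table and some data entry, which can be confined to low readings and the count of readings. Meters, strips and training are already planned. The drawback is that the logs are self-recorded by unblinded patients and may be incomplete. Giving the number of readings by arm makes uneven testing visible but does not remove it.
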